#### **6.4 Adverse events (other than treatment failure)**

a) If a patient is unable to tolerate the trial medication the reason for discontinuation will be recorded in the Clinical Record Form as an “adverse event” and alternative rescue medication initiated.

b) Any clinical or laboratory abnormality which in the opinion of the senior attending clinician might be or is likely to be due to the study medication will be recorded as an adverse event.

Quinine at a dose of 10-mg/kg body weight will be the rescue medication for those who require it.

Adverse events will be classified according to:

|                                     |                                                                                                                                                           |
|-------------------------------------|-----------------------------------------------------------------------------------------------------------------------------------------------------------|
| Severity                            | a) non-severe, b) severe                                                                                                                                  |
| Causality in relation to medication | a) not related, b) unlikely to be related, c) possibly related, d) probably related, e) most probably related, f) insufficient data/information to assess |

Subjects with an AE will be followed up until the condition has disappeared or stabilized.

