### **4. TRIAL DESIGN**

#### **4.1 Primary end point**

The primary end-point of the trial will be treatment failure by day 28. This will be defined as:-

*Any of:-*

- 1) a need for rescue treatment due to clinical deterioration defined by altered sensorium, convulsions, persistent vomiting, renal impairment, respiratory distress, a fall in Hb below 7g/dl, or in cases where initial haemoglobin was less than 9 g/dl a drop of 20% from the starting Hb, at any time during admission;
- 2) persistence of fever with parasitaemia on day 3;
- 3) increasing parasite load on day 3;
- 4) failure to clear parasites on day 7;
- 5) rescue medication for recurrent malaria before day 28;
- 6) slide parasite positivity at day 28.

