### 5.4 Withdrawal criteria

Withdrawal criteria will include:-

---

\* prior chloroquine ingestion will not be an exclusion criterion. Drug ingestion in the previous 2 weeks will be ascertained by patient interview as full testing for all locally available drugs with antimalarial activity is not feasible.

1. withdrawal of consent or non-compliance with assigned study regimen;
2. appearance of other species of *Plasmodium*;
3. vomiting within one hour after re-dosing;
4. protocol violation.

If it is necessary to withdraw a patient during the treatment phase, administration of the study drug will be discontinued. If the patient is still parasitaemic, quinine will be given as a rescue therapy unless there are clinical reasons to use another drug. For withdrawals outside the treatment phase the team will carry out all the safety and efficacy assessment measurements that would have been carried out at the next scheduled visit and the same will apply at delivery (unless the patient is lost to follow up). In such cases the study conclusion page in the Clinical Report Form will be completed and the study medication records updated. Patients withdrawn from the study will continue attending routine antenatal care provided by the MCH clinic. Finger prick blood smear for microscopy and Hb. will be done at every withdrawal. If rescue treatment is given, the blood smear will be checked again on day 7 post-treatment to ascertain parasitological clearance. Patients withdrawn before day 7 and not classified as treatment failures will be replaced.

5) Patients who fail on treatment will be treated with rescue treatment and counted as treatment failures (see above).

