## **6.3 Clinical treatment and investigations.**

All women enrolled will be admitted to the research ward (to be built by the GMP) for the first three days for DOT and to monitor clinical response and adverse events. Drugs will be administered by nurses employed by the project. After each administration, the patient will be observed for 45-60 minutes to ascertain drug retention. The dose will be repeated if vomiting occurs within the observation period, and any further vomiting will cause withdrawal from the study and treatment with parenteral quinine. Patients will be treated for symptoms by standard treatment e.g. paracetamol for fever. Women will also continue to receive routine antenatal medicaments of iron supplements, folic acid, and Tetanus Toxoid (TT) given by the MCH. Drugs with an antimalarial activity will not be permitted; if these are essential, the subject will be withdrawn.

Vital signs (temperature, pulse) will be monitored eight hourly during the treatment period and once daily during the remaining period of hospitalisation. Blood pressure will be measured once daily during hospitalisation. Patients will be interviewed using a “clinical assessment form” check list which includes: weakness, chills/rigors, headache, myalgia, dizziness, abdominal pain, anorexia, nausea, vomiting, diarrhoea, palpitations, insomnia, pruritus, coughing, and tinnitus. Blood glucose will be measured on admission and regularly through treatment by glucose stix testing.

Foetal viability (presence of foetal heartbeat) will be monitored daily during admission using a Doppler machine, and at each follow-up visit.

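### Item 1 of the primary endpoint can score possible drug toxicity as antimalarial failure, and the protocol does not ensure that the same event is also recorded as an adverse event

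*Protocol*

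**What the plan says.** **Primary endpoint (section 4.1).** Any one of six criteria makes a treatment failure. Item 1 is "a need for rescue treatment due to clinical deterioration defined by altered sensorium, convulsions, persistent vomiting, renal impairment, respiratory distress", or a haemoglobin fall to under 7 g/dl. Its other haemoglobin criterion reads "in cases where initial haemoglobin was less than 9 g/dl a drop of 20% from the starting Hb, at any time during admission". It names no parasite finding. The other items do name parasites or malaria; item 2, for example, is "persistence of fever with parasitaemia on day 3".

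**Adverse events (section 6.4).** The heading reads "Adverse events (other than treatment failure". On intolerance, (a) reads: "If a patient is unable to tolerate the trial medication the reason for discontinuation will be recorded in the Clinical Record Form". The entry is made as an adverse event, and rescue medication is started. Item (b) concerns suspected effects of the study drug and covers "Any clinical or laboratory abnormality which in the opinion of the senior attending clinician might be or is likely to be due to" that drug. Severity and causality are then graded, and the causality scale includes a not-related category.

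**Vomiting and withdrawal (sections 6.3 and 5.4).** A dose vomited within the observation period is repeated, after which "any further vomiting will cause withdrawal from the study and treatment with parenteral quinine". Section 5.4 adds: "Patients withdrawn before day 7 and not classified as treatment failures will be replaced".

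**Schedule (Appendix 1).** Adverse event review is ticked on days 0, 1, 2, 7, 14, 21 and 28 and at delivery, but not in the column for the time of treatment failure. Blood smears are ticked in that column.

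**The concern.** The trial is meant to assess efficacy and safety of each regimen (section 3). Most of the item-1 triggers are also ways in which a poorly tolerated drug would show itself. If rescue for such an event is scored as antimalarial failure whatever the smear shows, a regimen that clears parasites can look less effective than it is. If the event is then treated as belonging to efficacy only, the by-arm adverse-event analysis in section 11 may not show it.

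For vomiting and intolerance the label matters more. It decides whether a woman counts as a failure, or is withdrawn and another woman enrolled in her place.

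**Working it through.** **1. Parasite or malaria condition in each criterion of section 4.1**

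| Item | Condition |
|---|---|
| 1 | none stated |
| 2 | parasitaemia on day 3 |
| 3 | parasite load on day 3 |
| 4 | parasites on day 7 |
| 5 | recurrent malaria |
| 6 | slide on day 28 |

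Item 1 stands alone. It is limited to the admission, which section 6.3 sets at the first three days.

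**2. Would an item-1 event reach the safety data?** Take a smear-negative woman whose haemoglobin falls on the ward and who is given rescue.

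- From 9.5 to 6.9 g/dl: below 7, so item 1 is met. The fall is 9.5 − 6.9 = 2.6 g/dl.
- From 8.5 to 6.8 g/dl: (8.5 − 6.8)/8.5 = 1.7/8.5 = 20%, so item 1 is met.
- The haemoglobin triggers for DSMB notification in section 9 are a fall of more than 4 g/dl or a value below 5 g/dl. Neither case meets them.
- Each woman therefore enters the adverse-event data only if the attending clinician thinks the drug might be the cause (6.4(b)). That clinician is not stated to be blind; section 4.3 blinds only the slide reader. Section 9 already presumes that most of the large falls it describes come from the disease.

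**3. Three labels for vomiting or intolerance with rescue**

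| Section | Label | Consequence |
|---|---|---|
| 4.1 item 1 | treatment failure | counts in the primary endpoint |
| 6.4(a) | adverse event, rescue started | endpoint status not stated |
| 5.4 and 6.3 | withdrawal, quinine | replaced if before day 7 and not a failure |

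No rule says which label prevails, or that two can hold together. Section 11 bases the primary analysis on women with at least one dose, so a withdrawn woman who was dosed still needs an endpoint status.

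**4. Size.** Inputs from the October 2004 revision in the sample-size section: failure rates 1% and 15%, alpha 0.05, stated β of 0.8 read as 80% power, 72 per arm.

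Reproducing 72 (two-sided):

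- n = [1.96·√(2·0.08·0.92) + 0.842·√(0.01·0.99 + 0.15·0.85)]² / 0.14² = (0.752 + 0.312)²/0.0196 ≈ 57.8, that is 58.
- With continuity correction: (57.8/4)·[1 + √(1 + 4/(57.8·0.14))]² ≈ 71.3, that is **72**, as stated.

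Expected failures are 0.01 × 72 = 0.7 and 0.15 × 72 = 10.8 women. One smear-negative item-1 event is 1/72 = **1.4 percentage points**, more than the whole planned rate of the best arm. Three such women (an assumption) would give (0.7 + 3)/72 ≈ 5%.

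Sensitivity: let t be the rate of item-1 events without parasites, so that the failure rate becomes p + (1 − p)t. The documents give no t, so every row is an assumption. Required n uses the continuity-corrected formula; power at 72 uses the uncorrected one.

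| t | Best arm, events there only | n per arm | Power at 72 | n per arm, same t in both arms |
|---|---|---|---|---|
| 0 | 1.0% | 72 | 88% | 72 |
| 1% | 1.99% | 86 | 81% | 79 |
| 2% | 2.98% | 104 | 72% | 87 |
| 3% | 3.97% | 128 | 62% | 95 |
| 5% | 5.95% | 201 | 43% | 112 |

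If such events fell mainly in the less effective arm, the difference in failure would widen instead.

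**The case against.** A reader might infer that section 6.4 defines adverse events so as to exclude treatment failures, that toxicity therefore drops out of safety, and that efficacy and safety are distorted in opposite directions. The documents do not support this. The exclusion is only a parenthesis in a heading. The operative sentence, 6.4(b), makes no exception for women who are also failures. Section 9 sends all serious possible side effects to the DSMB, and the ethics section gives the DSMB both adverse events and treatment failures. Section 6.3 puts a symptom checklist that includes vomiting to the patients, and section 11 plans an adverse-event analysis. The word Other in the last secondary endpoint reads naturally as other than the safety items already listed there.

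The unticked box in Appendix 1 also carries limited weight. Item 1 applies during admission, and adverse event review is ticked on each of days 0, 1 and 2.

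Counting early deterioration that needs rescue as failure is a legitimate composite in women enrolled with parasitaemia. A split by smear result could properly sit in an analysis plan that is not shown, so its absence is not the finding.

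All of this stands, and it reduces the safety part from a loss to a possible omission. It does not supply a parasite condition for item 1, a statement that one event can be both failure and adverse event, or a rule for vomiting and intolerance. DSMB reporting serves monitoring during the trial; it does not by itself place an event in the final by-arm table.

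**Conclusion.** The point holds in a limited form. As written, item 1 allows possible drug toxicity to be scored as antimalarial failure, and the same event may be missed in the adverse-event tabulation when the clinician does not suspect the drug. The passages on vomiting and intolerance conflict and must be reconciled.

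The firm figure is 1.4 percentage points per event at 72 per arm, against a planned 1%. Anything larger, including the three-women illustration and the sensitivity table, rests on an assumed event rate and on which arm the events fall in. The sample size of 72 is not in error. The text does not support a claim that adverse-event counts must fall.

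**What to change.** Keep the composite primary endpoint and change the following:

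1. Remove the parenthesis from the 6.4 heading and state that an event can be both a treatment failure and an adverse event.
2. Record every item-1 event as an adverse event on the existing severity and causality scales, and tick adverse event review in the treatment-failure column of Appendix 1.
3. Report item-1 failures by arm and by smear result on the day of rescue, with a sensitivity analysis in which smear-negative item-1 events are not counted as antimalarial failure. This may be placed in section 11 or in the analysis plan.
4. Reconcile sections 4.1, 5.4, 6.3 and 6.4(a) on vomiting and intolerance so that each woman has one defined primary-endpoint status. Which status applies is for the investigators to decide.

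The cost is a few lines of text and one table. Smears are already taken each morning on the ward (section 6.5) and at treatment failure (Appendix 1). Some events will appear in both the efficacy and the safety tables, which a footnote can explain. A positive smear early in admission does not rule out a drug effect, so the sensitivity analysis removes only the clearest cases; the causality grade covers the rest.

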## **4.3 The trial**

1. This will be a randomized controlled trial with four arms;
2. The slide reader assessing the primary endpoint will be blind to treatment allocation, and analysis will be performed by intention-to-treat;
3. Direct Observed Therapy (DOT) of all doses of study regimens will be employed;
4. Drug doses packed in blister packs, labelled with the patient number will be used where possible.

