## **6.2 Regime allocation**

Women will be randomized in blocks of ten (each block with 1 SP group and 3 each of the other three groups). Random numbers between 1 and 800 will be generated by the computer (EPI INFO) programme and allocated to regimens until 80 numbers are in the SP+ placebo group and 240 each in the three other treatment groups. On consenting to participate, patients will be registered numerically in the enrolment log as they present. The registration number will determine the drug regimen.

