## **9 Stopping rules/discontinuation criteria (finalised after meeting of the DSMB)**

*Parasite clearance:* The study has to balance the Tanzania government's recent policy to use SP as first line drug treatment against a high SP-resistance in Muheza district. We assume that around 45% of women in the SP group will need escape medication. Since all women will be admitted to the study ward, the escape medication will be administered on time and complications arising from the use of a relatively ineffective drug should be minimal. However, if the proportion of women needing escape medication is  $\geq 40\%$  in any arm of the study, we will discontinue that arm when 50 women are enrolled which will give a confidence limit of 25-55% for the estimated treatment failure rate.

*Side effects.* All serious possible side-effects and foetal deaths will be faxed to the DSMB statistician. All other adverse events will be forwarded. The DSMB (see section on ethics) will decide on whether one arm, or the whole study, needs to be terminated. Suggested guidelines for this following the first meeting of the DSMB is that the DSMB would take note following one SAE in an arm, and consider whether an arm needed to be terminated after 2, but would review in the light of data at that stage. The DSMB wishes to be informed if there is a fall in haemoglobin of  $>4$  g/dl, OR where haemoglobin falls below 5 g/dl and these will be treated as a potential SAE, but since most such drops will be secondary to the natural history of the disease these will be noted and discussed, but treated differently from other SAEs.

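### Section 6.4(b) makes suspected drug causality the condition for recording an abnormality as an adverse event, which contradicts the section's own causality scale and can bias or dilute the 'other adverse events' comparison

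*Protocol*

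**What the plan says.** Protocol section 6.4 gives two routes by which something becomes an adverse event.

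- Limb (a) covers intolerance: "If a patient is unable to tolerate the trial medication the reason for discontinuation will be recorded in the Clinical Record Form". Such a discontinuation counts as an adverse event.
- Limb (b) covers everything else. A clinical or laboratory abnormality which the senior attending clinician believes "might be or is likely to be due to the study medication will be recorded as an adverse event".

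The table that follows in 6.4 classifies adverse events by relation to medication: "a) not related, b) unlikely to be related, c) possibly related, d) probably related, e) most probably related", plus a class for insufficient information.

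On blinding, section 4.3 states: "The slide reader assessing the primary endpoint will be blind to treatment allocation". Nothing is said about the attending clinician. Section 6.1 lists a single-dose regimen and three 3-day regimens and mentions no placebo, but section 6.2 allocates numbers "until 80 numbers are in the SP+ placebo group and 240 each in the three other treatment groups", and the original sample size text also refers to SP with placebo.

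Adverse events are a secondary endpoint (4.2 item 11, other adverse events during treatment) and a pre-planned analysis (section 11). For the DSMB, section 9 states: "All serious possible side-effects and foetal deaths will be faxed to the DSMB statistician". It adds that all other adverse events are forwarded.

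**The concern.** A between-arm comparison of adverse events is protected by randomisation only if events enter the record in the same way in every arm. Limb (b) puts a judgement about the drug before the record. If the person judging knows the regimen, familiarity with SP or wariness of a newer combination can change how often the same event is written down. That can create a difference between arms or hide one. Even if the judgement is the same in every arm, it discards events that the clinician puts down to malaria or to pregnancy, and so lowers the chance of seeing a real difference.

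The rule and the scale also do not fit together. If limb (b) is followed, the two lowest causality classes should be almost empty. If those classes are meant to be used, limb (b) is not the recording rule. Two clinicians could read the section in opposite ways.

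Safety is a stated objective (section 3). Section 6.1 justifies the combinations partly on the ground that the trial looks actively for side effects, and the October 2004 sample size note says that the revised size can detect common adverse events. An event that is never recorded cannot be restored by an analysis plan.

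**Working it through.** **Step 1: what passes through the filter.**

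- Filtered: unsolicited clinical abnormalities, and the step by which an abnormal laboratory value becomes an adverse event, since limb (b) names both kinds. These feed 4.2 item 11 and the adverse event analysis in section 11.
- Not filtered, as endpoints in 4.2: foetal death by Doppler, hypoglycaemia requiring treatment, perinatal and neonatal mortality, neonatal abnormality, preterm delivery.
- Not filtered, as raw data: the 15-symptom checklist, glucose and daily foetal heartbeat (6.3); haematology, chemistry and urinalysis at admission, day 3 and day 7 (6.5). Section 11 lists no comparison of the checklist, and of the laboratory data only haemoglobin recovery at day 14.

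**Step 2: the plan's own figure.** The sample size note gives 72 per arm for 1% v 15%, α 0.05 and 80% power (printed as β 0.8). The two-sided formula, with p̄ = 0.08, is

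m = [1.960·√(2·0.08·0.92) + 0.842·√(0.01·0.99 + 0.15·0.85)]² / 0.14² = 57.8

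With continuity correction, n = (m/4)·[1 + √(1 + 4/(m·0.14))]² = 71.3, so 72. The figure reproduces and is not in dispute. It sets the arm size for the illustration.

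**Step 3: unequal attribution, no true difference.** Let π be the true risk in both arms and a₁, a₂ the fractions of events that the clinician attributes to the drug. Recorded risks are πa₁ and πa₂. The probability of p < 0.05 is the sum, over all pairs of counts (x, y) for which Fisher's two-sided test rejects, of Bin(x; 72, πa₁)·Bin(y; 72, πa₂). The documents give neither π nor a, so both are assumptions. With π = 30%:

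| Attribution, arm 1 v arm 2 | Recorded risk | Probability of p < 0.05 |
|---|---|---|
| 100% v 100% (no filter) | 30% v 30% | 3.3% |
| 50% v 60% | 15% v 18% | 5.1% |
| 50% v 70% | 15% v 21% | 11.3% |
| 50% v 80% | 15% v 24% | 21.6% |
| 40% v 80% | 12% v 24% | 39.6% |

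The unfiltered figure is below 5% because Fisher's test is conservative at this size.

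**Step 4: equal attribution, true difference.** Assume true risks of 20% v 40%.

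- All events recorded: power 69.7%.
- Half recorded in each arm, so 10% v 20%: power 31.6%.

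No bias between arms is needed for the filter to do harm.

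**The case against.** Several stronger readings are tempting, and the documents do not support them.

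- *The whole safety comparison rests on opinion.* It does not. The foetal, perinatal, neonatal, preterm delivery and hypoglycaemia endpoints are counted without attribution, and section 11 plans foetal viability and birth outcome separately. In a pregnancy trial these are central safety outcomes. Only the residual adverse event endpoint is exposed.
- *Events are recorded only if the drug is suspected.* That is true of limb (b), but limb (a) is a second route without the clinician-opinion wording. The lowest causality classes may also show that unrelated events were meant to be recorded, and 'might be' is a low threshold. The section contradicts itself; it is not unambiguously restrictive.
- *The clinician is unblinded.* This is an inference. It is the likelier reading, given the differing schedules and nurse-administered doses, but the unexplained placebo wording leaves some doubt. The text supports saying that the clinician is not stated to be blind.
- *The DSMB sees only suspected reactions.* It does not. Foetal deaths go to the DSMB regardless, the haemoglobin triggers are numeric, and Appendix 2 requires any SAE to be reported within 24 hours with causality described afterwards. Item 4 under Ethical Issues has the DSMB receive all adverse events. Non-serious events still reach it only if 6.4 has let them into the record.
- *Existing data repair the problem.* They do so in part: unfiltered counts by arm could be produced from the checklist and the laboratory panel. Unsolicited events outside both cannot be recovered.

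The attribution gaps in the illustration are also assumed. At a gap of 10 percentage points the false-positive rate is about the nominal 5%.

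What stands is the wording of limb (b), its conflict with the scale, and the effect on one secondary endpoint.

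**Conclusion.** The point holds for the general adverse event comparison (4.2 item 11 and the matching analysis in section 11) and no further. Section 6.4(b) makes suspected causality, judged by a clinician not stated to be blind, the condition for recording an abnormality, and this contradicts the causality scale in the same section.

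The size cannot be read from the documents. Under the assumed 30% true risk and 72 per arm, false significance runs from about 5% with a 10-point attribution gap to about 40% with a 40-point gap. Equal attribution of one half would more than halve the power for a true 20% v 40% difference. These figures show sensitivity and are not a forecast. They also assume that limb (b) is applied literally. If staff record unrelated events, as the scale suggests, the loss is smaller but the practice departs from the rule.

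This should be corrected. It affects a secondary endpoint, the remedy is cheap, and the loss cannot be fully made good after data collection.

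**What to change.** - Reword 6.4(b) so that every new or worsening clinical or laboratory abnormality after the first dose is recorded as an adverse event regardless of suspected cause, and is then graded on the existing causality scale.
- In section 11, make the all-cause comparison by arm the main adverse event analysis and the comparison of drug-attributed events secondary.
- In section 9, replace the reference to serious possible side effects with 'serious adverse events', so that it agrees with item 4 under Ethical Issues and with the SAE rule in Appendix 2.

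The cost is somewhat more case record entries. No visit or test is added, because the schedule in Appendix 1 already has an adverse event review at each scheduled visit to day 28 and at delivery.
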